# Cognitive effectiveness of high-intensity interval training for individuals with methamphetamine dependence: a study protocol for randomised controlled trial

**DOI:** 10.1186/s13063-021-05615-9

**Published:** 2021-09-23

**Keywords:** Methamphetamine, High-intensity interval training, Moderate-intensity continuous training, Cognitive function, Inhibitory control

## Abstract

**Introduction:**

Cognitive deficit is a common syndrome of methamphetamine (MA) dependence. It is related to decision-making, control ability, and social functioning. High-intensity interval training (HIIT) is a training technique that requires people to work out at full intensity during a short period. Many studies have already shown the potential effects of HIIT on cognitive functions. The purpose of this trial is to evaluate the cognitive effects of HIIT on individuals with MA dependence.

**Methods and analysis:**

A total of 240 individuals with MA dependence will be randomly assigned to the HIIT group, moderate-intensity continuous training (MICT) group and control (CON) group. HIIT will consist of a 24-min HIIT exercise on a treadmill. MICT will consist of a 1-h body–mind exercise. CON will be their traditional intervention. The experimental period will be 12 months with 3 interventions weekly for the first 6 months and follow-up for the next 6 months. All subjects will be given cognitive tests at baseline, after intervention and at follow-up. Cognitive performances will be compared by a mixed-model analysis for repeated measures.

**Discussion:**

HIIT training may reduce illicit drug cravings amongst individuals with MA dependence; hence, HIIT may have a good effect on the cognitive functions, such as memory and executive function, of individuals with MA dependence.

**Trial registration:**

Chinese Clinical Trial Registry ChiCTR2000032492. Registered on April 30, 2020 (http://www.chictr.org.cn/edit.aspx?pid=52127&htm=4)

## Introduction

Substance abuse is a growing public health concern worldwide that causes negative influences to the health of abusers and leads to the occurrence of illegal and criminal behaviours. Methamphetamine (MA) consumption has risen rapidly in the past few years with an estimated annual prevalence of 0.7% worldwide [85]. By the end of 2019, 2.1 million drug dependents in China have been recorded; amongst whom, 1.2 million were individuals with MA dependence [71]. Compared with traditional illicit drugs, such as opium and heroin, MA causes greater harm to the human body [32]. Besides arousing users’ strong mental dependence, MA also directly affects the central nervous system and causes irreversible damage [58, 98]. Numerous long-term MA users suffer consequences, such as physical illness, mental health, social adjustment and poor mental symptoms [48, 80]. These consequences may be because MA disrupts the prefrontal striatum dopamine pathway involved in various cognitive and psychomotor processes, including behavioural decision-making [55]. Long-term MA use can lead to a series of cognitive deficits [12, 96]. Amongst which, the most serious are related to reward or impulsiveness and social cognition [73]. Such deficits are associated with decision-making disorders caused by drug addiction [70]. Unlike normal subjects, those who have used MA for more than 5 years have a defect in decision-making ability in balancing reward and punishment [55]. MA use changes the decision-making ability by altering the value perception of reward and negative results [68], which could lead addicts to continue to make negative decisions despite the potential hazard of the reward stimulus [95]. Thus, drug users tend to lose control of their drug-taking and drug-seeking behaviours [69]. Data from several Stroop tests, including alcohol, cocaine, nicotine and internet addiction, pointed out that compared with the normal control group or patients with light symptoms, addicts have poorer concentration, reaction time and accuracy under addiction-related stimulus (such as drug pictures), which represent their poor inhibitory control [26, 31, 35, 45, 61]. Similarly, another research showed that individuals with MA dependence have delayed cognition, misjudgement and poor cognitive control in the Stroop test using MA-related words as irrelevant stimuli [20]. Another drawback of long-term MA use is attention deficit [7]. MA and cocaine dependents show worse attention in the Stroop test than healthy control subjects [50, 79]. In summary, individuals who are chronically exposed to illicit drugs experience difficulties in execution, inhibition and decision-making [7].

Exercise as a supplementary treatment for substance abuse has been favoured and concerned by many countries [2]. Exercise can reduce withdrawal symptoms and the possibility of relapse [13, 83]. Theoretical and empirical studies have found that short- and long-term moderate-intensity aerobic and resistance exercise may remarkably improve the brain cognition, psychological behaviour and physical function of the drug-dependent group, as well as ameliorate their life quality and drug craving [62, 89]. One study found that the mental health of heroin dependents is promoted after 6 months of aerobic exercise; the effect of aerobic exercise intervention appears at 3 months, whereas yoga exercise needs 6 months to take effect [81]. Another study [90] manifested lower levels of craving and greater accuracy in behavioural inhibition control in individuals with MA dependence who underwent aerobic exercise for 12 weeks. Cardiovascular function and physical condition are remarkably improved, the nervous system tends to balance and the inhibitory ability of MA and drug craving are ameliorated in amphetamine-type synthetic drug dependents after 6 months of tai chi (TC) intervention [49, 66, 97].

High-intensity interval training (HIIT) is a relatively short repetitive training performed in an ‘all-out’ manner at an intensity that can cause VO_2_ peak and usually lasts from 10 s to 4 min with short intervals [15, 40]. HIIT is able to achieve a certain physical activity level in a shorter time than traditional aerobic exercise or physical activity. HIIT is a recently popular form of full-body aerobic exercise that includes various exercises, such as running and roping. Aerobic exercise has a preferable influence on cognitive function, including memory and reaction time [6, 60], and the effect of HIIT on physical and mental health is more helpful than moderate-intensity continuous training (MICT). Besides, exercises of different intensities have disparate effects on cognitive function; a study showed that cognitive function is enhanced immediately after a high-intensity workout [6]. A meta-analysis also found that executive effects, including inhibitory control and memory task, tend to improve during a series of cognitive tasks within a period of time after acute high-intensity exercise [18]. Additionally, the positive effect of acute high-intensity exercise on cognitive performance is more persistent than that of MICT [18]. Some studies suggest a positive correlation between exercise intensity and cognitive function [30, 34, 54]. Moreover, the effects of aerobic exercise on cognition depend on exercise intensity [36]. Notably, as an important cognitive mechanism, increasing research has linked inhibitory control with higher cognitive functions [41, 91]. Poor inhibition control is likely an element in the maintenance of addiction [87] and a key factor in the prediction of the successful recovery of addicts [9, 32, 35, 38]. Physical activity has a host of potential advantages in addiction treatment [2, 93]. However, drug addicts have difficulties in adhering to a certain type of exercise for long periods of time because of comorbid cognitive and mental health problems [2]. Together, these studies indicate that the results of exercise intervention will be affected, and HIIT can solve this issue to some extent owing to its less time consumption.

Investigations on MICT and HIIT to improve cognitive function have recently gained much attention. Although a few studies explored the effects of HIIT on drug-dependent animals [47], research on the cognitive effects of HIIT on drug dependents, especially MA dependents, is lacking. The aims of this trial are to (1) determine whether HIIT improves the cognitive function of individuals with MA dependence, (2) determine whether HIIT reduces drug craving and improves the mental health of individuals with MA dependence and (3) compare the cognitive rehabilitation effects of HIIT and MICT on individuals with MA dependence. We hypothesise that (1) HIIT and MICT interventions will be effective in improving the cognitive functions of MA dependents compared with the control group and (2) the effect of HIIT will be better than the other two interventions (i.e. MICT and control).

## Methods

### Study design

This study is designed as a prospective, single-blind randomised controlled trial (RCT). The overview of the trial is displayed in Fig. 1.

**Fig. 1 Fig1:**
[figure not shown]
Flow diagram of the study design

**Fig. 2 Fig2:**
[figure not shown]
Schedule of enrolment, interventions and assessments

### Participants

#### Inclusion criteria

The patients must meet the following criteria for inclusion in the study: (1) age between 18 and 40 years, (2) drug dependence diagnosed according to the Chinese Classification of Mental Disorders 3, (3) remaining withdrawal time of more than 1 year, (4) absence of serious medical or mental illness, (5) primary school education or higher, (6) compulsory drug treatment and (7) volunteered to participate in this study.

#### Exclusion criteria

The patients will be excluded if they have any of the following: (1) participation in HIIT before the present study, (2) other diseases that may interfere with the implementation of the research programme, such as heart, lung, liver and kidney diseases, musculoskeletal, dysfunction or cancer, (3) antisocial personality disorder and borderline personality disorder, (4) severe cognitive, visual or auditory impairment and (5) unstable medication.

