### Study assessments

#### Participants’ characteristics

The demographic and health characteristics of subjects will be collected at baseline (Table 1). The characteristics will include age, gender, education, marital status, drug abuse years, type of drug use, whether exercise, weight (kg), height (cm), body mass index, blood pressure (mmHg) and lung capacity (ml). Automatic equipment (Omron sphygmomanometer), electronic digital scales and electronic lung capacity tester will be used to measure blood pressure, weight, height and lung capacity, respectively.

**Table 1 Tab1:** Demographic and characteristics of participants

	HIIT (*n=80*)	MICT (*n=80*)	CON (*n=80*)
Age			
Gender			
Education			
Marital status			
Drug abuse years			
Types of drug use			
Whether exercise			
Weight (kg)			
Height (cm)			
BMI			
Hypertension (mmHg)			
Pulmonary (ml)			

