### Primary outcome assessment

#### Stroop test

Stroop is one of the most widely used neurocognitive tasks [63, 67] and as a tool to assess the efficiency of inhibition mechanisms and explore the relationship between inhibition and impulsivity [72]. Individuals with substance use disorders have lower baseline metabolic activity in the prefrontal cortex (PFC), which is associated with impaired cognitive function in decision-making and inhibitory control [4, 11]. The cognitive portion of the Stroop test has been used as a psychometric test to assess cognition as it is related to executive function in decision-making and inhibitory control related to PFC exercise.

The experimental materials are ‘RED’, ‘GREEN’ and ‘BLUE’ characters written in Chinese, and conditions will be classified as congruent and incongruent (Table 2). Congruent condition means that the font colour is in line with its literal meaning, whereas incongruent condition means that the font colour disagree with its literal meaning. Participants will be asked to respond to the colour of the word through the following instructions: press ‘J’ key if the colour of the Chinese character is red, press ‘K’ if it is s green and press ‘L’ if it is blue. Keys ‘J’, ‘K’ and ‘L’ correspond to the index finger, middle finger and ring finger of the right hand, respectively. At the beginning of the experiment, the fixation point ‘+’ will be presented in the centre of the screen for 500 ms, and then the experimental stimulus is presented. Participants will be required to identify the colour of the stimulus on the premise of ensuring correct reflection and then use the right finger to make a response. Stimulus words last for 1000 ms or disappear after pressing the button, and then the next test will start after 500 ms.

**Table 2 Tab2:** Primary outcome of the three groups

	HIIT (*n=80*)			MICT (*n=80*)			CON (*n=80*)		
	Pre	Post	Follow-up	Pre	Post	Follow-up	Pre	Post	Follow-up

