**Symbol search**									
Symbol searched total									

The whole task will be divided into two parts. The first part has a feedback, whereas the latter part has no feedback. The four stages will comprise 40 trials each in formal trials with a 30-s break in between. The three-colour words will be randomly presented to the participants for 24 times, and the symbols of red, green and blue are presented for 16 times. Each subject will receive a total of 120 tests. Response time and accuracy will be recorded at each stage. These two indicators represent an individual’s inhibition control ability (Fig. 3).

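### The Stroop task needs red, green and blue ink to be told apart, but eligibility excludes only severe visual impairment, so colour-vision errors can be scored as poor inhibition

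*Protocol article*

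**What the plan says.** **The task.** Under Primary outcome assessment, Stroop test, the protocol article states: "Participants will be asked to respond to the colour of the word through the following instructions". The instruction runs "press ‘J’ key if the colour of the Chinese character is red, press ‘K’ if it is s green and press ‘L’ if it is", the last colour being blue. Stroop scores stand in Table 2, "Primary outcome of the three groups", beside digit span and symbol search, with no ranking among the three. The text after Table 2 takes response time and accuracy as measures of inhibitory control. It also mentions non-colour-word material: "the symbols of red, green and blue are presented for 16 times". The Statistical analysis section analyses congruent and incongruent reaction time and accuracy by time point and group.

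**Eligibility.** The single vision clause, exclusion 4, covers "severe cognitive, visual or auditory impairment". Two other clauses might be thought relevant:
- inclusion 4: "absence of serious medical or mental illness";
- exclusion 2: "other diseases that may interfere with the implementation of the research programme", with organ disease, musculoskeletal problems and cancer as its examples.

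**Baseline data.** Under Participants' characteristics: "The characteristics will include age, gender, education, marital status, drug abuse years, type of drug use", followed by exercise habit, body measurements, blood pressure and lung capacity. Colour vision is not listed.

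**The concern.** The eligibility list is printed in full and already has a vision clause. That clause is set at a level that misses the one visual ability on which the Stroop response depends. Someone with red-green deficiency and normal acuity does not have severe visual impairment, so a site applying the list literally would enrol that person.

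The error can also resemble the construct being measured. On a congruent trial the word names the correct key even when the ink is ambiguous. On an incongruent trial the word points to the wrong key. A participant who leans on the word when unsure of the ink will look normal on congruent trials and poor on incongruent ones, which is the pattern expected from weak inhibition. Subtracting congruent from incongruent reaction time (the interference cost in Table 2) need not remove it. For such participants the Stroop scores partly measure colour vision, and this enters a primary outcome.

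**Working it through.** The plan has no figure of its own to reproduce on this point, so what follows only gauges size.

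**From the protocol article:** three ink colours; 80 per arm, 240 in total; 10% attrition, hence 240 × 0.9 = 216 completers; effect size 0.28; α = 0.05.

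**Assumed, not in the documents:** the six incongruent word–ink pairings (3 inks × 2 non-matching words) are equally frequent; the affected person cannot separate red from green ink at all, always recognises blue, and would otherwise score 100%; prevalence *p* of 5%, with 1%, 4% and 8% as a range.

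**Score of one affected participant**

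| Behaviour on red or green ink | Incongruent accuracy | Congruent accuracy | Gap |
|---|---|---|---|
| Guesses red or green whatever the word | (2 + 4 × 0.5)/6 = 67% | (1 + 0.5 + 0.5)/3 = 67% | 0 |
| Follows the word if it says red or green, otherwise guesses | (2 + 0 + 2 × 0.5)/6 = 50% | 3/3 = 100% | 50 points |

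The loss in incongruent accuracy is therefore 33–50 points, and the spurious gap 0–50 points. Each row must be read with its own congruent score.

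**Group level, one time point, *p* = 5%**
- Fall in mean incongruent accuracy: 0.05 × 33 to 0.05 × 50 = 1.7–2.5 points. At 1% it is 0.3–0.5 points, at 4% 1.3–2.0, at 8% 2.7–4.0.
- Between-person SD component: √(0.05 × 0.95) × 33–50 = 7.3–10.9 points.
- Chance imbalance between two arms: √(2 × 80 × 0.05 × 0.95) = 2.76 persons, or 3.4% of 80. Multiplied by 33–50 this is an SD of 1.1–1.7 points.
- Dilution: if affected participants show a share *r* of the training effect, the average effect is multiplied by 1 − *p*(1 − *r*). With *r* = 0 this is 0.95. With *r* = 2/6 (only blue-ink trials respond) it is 1 − 0.05 × 0.67 = 0.97.

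**Numbers affected and power over the range.** Expected count is 240*p*. Outcome variance is multiplied by 1 + *p*(1 − *p*)*s*², where *s* is an assumed shift in SD units. Power is for a one-way three-group F-test with 216 completers and f = 0.28, and is 0.964 with nobody affected.

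| *p* | Affected of 240 | Chance that two arms differ by 4 or more | Power, *s* = 2 | Power, *s* = 3 |
|---|---|---|---|---|
| 1% | 2.4 | 1% | 0.957 | 0.949 |
| 4% | 9.6 | 15% | 0.936 | 0.894 |
| 8% | 19.2 | 30% | 0.906 | 0.817 |

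These power figures treat the whole shift as error at a single time point. The planned Stroop analysis compares pre-test with post-test, so a stable offset largely drops out and the real loss should be smaller. Guessing noise and reduced response to training do not drop out.

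**The case against.** The strongest reply is that the effect on the trial's inference is small. Allocation is randomised, and the Stroop analysis is time by group, so a fixed trait present at both visits largely cancels. Most of the 7.3–10.9 point SD component is then outside the error term that matters. This stands, and it limits the weight of the point.

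The size model is also a worst case. The documents give no hue or luminance for the stimuli, the Stroop figure is not shown, and the Introduction describes poor Stroop performance in this population, so 100% is a generous comparator. This stands too.

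A reader might go further than the documents allow in several ways:
- *That the arms are biased.* Randomisation gives no reason to expect it; only chance imbalance remains.
- *That every affected person shows a large false interference effect.* Someone who guesses regardless of the word shows no gap.
- *That congruent accuracy can never expose the problem.* It fails to do so only when the person follows the word; under guessing it falls to 67%.
- *That affected participants cannot respond to training.* Blue-ink trials are answered normally, and mild deficiency leaves more intact.
- *That the lead primary outcome is compromised.* Table 2 ranks none of its three tests, and digit span and symbol search as described do not use colour.

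Finally, task-level checks may sit in a fuller protocol or test manual, and an investigator could stretch exclusion 2 to cover colour deficiency. But the criteria are given as a complete numbered list with a vision clause in it, and nothing in that list calls for a colour check. The issue is a criterion drawn too narrowly, which is different from a detail left to another document.

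**Conclusion.** The point holds in a limited form. As written, the criteria admit people who may be unable to perform the colour judgement that one of the three primary tests requires, and their errors can be scored as poor inhibition. The consequences are weaker construct validity, extra noise, some dilution and possible chance imbalance, all confined to the Stroop test.

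The 50–67% incongruent accuracy, the 0–50 point gap and the fall of at most about 1.7–2.5 points in the mean rest on wholly inseparable inks, otherwise perfect scores, equally frequent pairings and an assumed 5% prevalence. Partial deficiency would give less, and the pre–post comparison removes much of a stable offset. This does not threaten the trial's main conclusions, but it is worth correcting because the correction is so cheap.

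**What to change.** Add to the exclusion criteria: *inability to distinguish the red, green and blue stimuli of the Stroop task*. Check it before randomisation with word-free colour stimuli or a brief colour plate. Do not rely on congruent-word accuracy alone, since following the word hides the problem. The task's own red, green and blue symbols might serve, but the text after Table 2 says neither that they are word-free nor that they fall in the part with feedback. Confirm both before using them.

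The Trial status section reports recruitment as ongoing, so the criterion could still cover later entrants. For participants already enrolled, apply the same check, which can be done late because colour deficiency is usually a stable trait. Keep them in the main analysis and report a Stroop sensitivity analysis without those who fail.

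Cost: one line of text, a minute or so per person, and the loss of a few percent of volunteers at the prevalence assumed here.

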#### Dropout and suspension criteria

Subjects will have the right to withdraw from the study at any time during the intervention period. When they feel uncomfortable during the intervention, they can withdraw from the present study according to medical advice. Additionally, the subject will be excluded if an unexpected worsening of motor or neuropsychiatric symptoms occur.

### Randomisation and blinding

The study was designed as a single-blinded RCT. Participants will be randomly assigned into three groups by two trained assessors who will not participate in the intervention. A sequence number will be generated by SPSS 25.0 under the ratio of 1:1:1. The numbers will be placed in a sealed envelope and randomly distributed to the participants. The instructors in each group will be blinded to the group allocation, including the control group, and the instructors should not know each other. This study will be unable to blind participants because of the differences in the intervention methods to be used in the three groups.

### Sample size calculation

Sample size estimation was conducted using G*Power V.3.1 (Franz Faul, Universitat Kiel, Germany). The purpose of this study is to examine the effects of HIIT on the major cognitive functions of MA dependents. However, informed preliminary data and empirical evidence on the effects of HIIT are lacking. Thus, we estimated the effect size in these power calculations using an estimated sample from published studies that compared the effects of HIIT and continuous training on cognitive function in healthy adults [65]. Specifically, we used the values of some variables within the ANOVA framework in this essay to obtain an effect size of 0.28 through the *t* test. Then, according to the *F*-test at *α* = 0.05 and power = 0.95, we obtained the required sample size of 223 subjects. The final average enrolment number with an anticipated 10% attrition rate is 240 (80 in each group) for the study to detect the difference in the cognitive outcomes between HIIT and MICT relative to the control group.

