### Statistical analysis

SPSS 25.0 will be used for statistical analysis. The descriptive outcomes will be displayed as mean ± standard deviation. The *F*-test will be applied to test the continuous variables, and the chi-square test will be used to test the classification variables. For the Stroop test, reaction time (congruent and incongruent) and accuracy (congruent and incongruent) will be analysed using 2 (time points: pre-test vs. post-test) × 3 (groups: HIIT vs. MICT vs. control) repeated-measures ANOVA. Other data will also be analysed using repeated-measures ANOVA. All post hoc tests will be corrected by Bonferroni for multiple comparisons. Intention-to-treat analysis will be used to process the missing data. The linear mixed model method will be applied to analyse all continuous variables with random missing values. The magnitude of the difference between fitness levels will be assessed by Hedges’ *g* [28], and the magnitude will be classified as small (0.2 < ES < 0.5), moderate (0.5 < ES < 0.8) or large (ES > 0.8). The significance level will be set at *p* < 0.05 for all analyses.

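### The 95% power uses an effect size of unstated metric and an F-test whose df match no planned group test, and it does not cover HIIT versus MICT

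*Protocol article*

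**What the plan says.** All sizing statements are in the protocol article, Sample size calculation. The effect size comes from "published studies that compared the effects of HIIT and continuous training on cognitive function in healthy adults". On its derivation the section says "we used the values of some variables within the ANOVA framework in this essay to obtain an effect size of 0.28 through the", naming a *t* test. The authors then turned to an F-test: "at *α* = 0.05 and power = 0.95, we obtained the required sample size of 223 subjects". Enrolment follows: "The final average enrolment number with an anticipated 10% attrition rate is 240 (80 in each group"). The closing sentence of the section gives the target as HIIT and MICT relative to control.

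The Introduction makes the comparison of HIIT with MICT the third aim. Hypothesis 1 is that both exercise arms beat control. Hypothesis 2 is that "the effect of HIIT will be better than the other two interventions (i.e. MICT and control").

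The Statistical analysis section plans a repeated-measures ANOVA with two time points and three groups for the Stroop outcomes, and repeated-measures ANOVA for the other data. On pairwise tests it says: "All post hoc tests will be corrected by Bonferroni for multiple comparisons".

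No power is stated for any pairwise contrast.

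**The concern.** A *t* test on a two-arm comparison most naturally yields a standardised mean difference, d. An ANOVA power calculation takes f, and for two equal groups f = d/2. If a d of 0.28 was entered as f, the assumed effect was doubled. If 0.28 was already an f, it matters whether it is an f for two groups or for three, because the two imply very different gaps between HIIT and MICT.

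Separately, a significant F-test across three arms does not show that HIIT beats MICT. That conclusion needs the pairwise test at the corrected alpha. A reader who sees 95% power will assume it applies to the trial's distinctive question and will weigh a non-significant HIIT–MICT result accordingly. The document gives no basis for that.

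**Working it through.** **Inputs.** Effect size 0.28, alpha 0.05, power 0.95, N = 223, enrolment 240 (80 per arm) and attrition 10% come from Sample size calculation. After attrition 240 × 0.9 = 216, or 72 per arm. Bonferroni over three pairs gives two-sided alpha 0.05/3 = 0.0167. The number of pairs is my assumption, so both 0.05/3 and 0.05 are shown.

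**Step 1: reproduce 223.** Non-central F with λ = f²N and f = 0.28, smallest N with power at least 0.95:

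| Numerator df | N |
|---|---|
| 1 | 168 |
| 2 | 201 |
| 3 | 223 (power 0.9501; 0.9491 at 222) |
| 4 | 242 |

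Repeated-measures options (two or three time points, correlation 0 to 0.8) and two-sample and paired *t* tests were also tried. Of the settings that keep 0.28 and three groups, only 3 numerator df gives 223. So 0.28 was evidently entered as f. The planned tests do not have 3 df: the group effect has 3 − 1 = 2, and the 2 × 3 interaction has (2 − 1)(3 − 1) = 2. With 2 df, power at f = 0.28 is 96.4% at 216, 96.9% at 223 and 97.8% at 240.

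**Step 2: if 0.28 is d.** Then f = 0.28/2 = 0.14. The three-group F-test has 43% power at N = 216 and 47% at N = 240, and needs N = 791 for 95%.

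**Step 3: HIIT–MICT gap under each reading.**
- 0.28 is d: gap 0.28 SD.
- 0.28 is f over three equally spaced means: f² = (2/3)·step², so step = √1.5 × 0.28 = 0.343 SD.
- 0.28 is f for the two-arm source comparison: gap 2 × 0.28 = 0.56 SD.
- 0.28 is f over three groups with MICT equal to control: f² = (2/9)·gap², so gap = √4.5 × 0.28 = 0.594 SD.

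**Step 4: pairwise power.** Two-sample non-central *t*, noncentrality gap × √(n/2), no baseline adjustment:

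| Gap (SD) | n = 72, 0.05/3 | n = 80, 0.05/3 | n = 72, 0.05 | n = 80, 0.05 |
|---|---|---|---|---|
| 0.28 | 23% | 26% | 39% | 42% |
| 0.343 | 36% | 40% | 53% | 58% |
| 0.56 | 82% | 87% | 92% | 94% |
| 0.594 | 87% | 91% | 94% | 96% |

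Only the last row reaches 95%, and only at n = 80 with uncorrected alpha.

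**Step 5: can a three-group f of 0.28 serve both hypotheses?** Let a be the HIIT–MICT gap and b the MICT–control gap. Then f² = (2/9)(a² + ab + b²), so a² + ab + b² = 4.5 × 0.0784 = 0.3528. The smaller of a and b is largest when a = b = 0.343. With the hypothesised ordering, at least one of these two contrasts therefore has power of 58% or less on unadjusted scores.

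**Step 6: pre/post correlation (not given, so assumed).** Taking 0.28 or 0.343 as being on the raw-score SD, baseline adjustment divides the gap by √(1 − ρ²). At ρ = 0.7, power across the same n and alpha range is 47–69% for 0.28 and 68–86% for 0.343. With two time points, the group × time test is a change-score test, with the gap divided by √(2(1 − ρ)). It leaves the Step 4 figures unchanged at ρ = 0.5. For 0.28 it gives 40–62% at ρ = 0.7 and 16–32% at ρ = 0.3.

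**Step 7: detectable difference.** At 80% power, 72 per arm, alpha 0.05/3, unadjusted: about 0.54 SD.

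**The case against.** The strongest reply is that the protocol never claims 95% power for HIIT versus MICT. Its stated target is HIIT and MICT relative to control. With f = 0.28 and equal spacing, HIIT versus control is 2 × 0.343 = 0.686 SD, with power 95–99%. This stands, and the point should not be read as saying that every contrast is underpowered. It does not help the MICT–control half of that target, which has the same 36–58% under equal spacing, and HIIT versus MICT is still a stated aim and hypothesis with no power attached.

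A second reply is that whether 0.28 is d or f depends on a source that is not at hand, and that the wording mentions both an ANOVA framework and a *t* test. This also stands. A reader might infer that power for HIIT versus MICT is simply 23–58%, close to a coin toss or worse. The document does not support that: the range joins two readings and omits the two-group f, which gives 82–94%.

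A reader might also infer that the 95% belongs to the three-group omnibus test. The text says only F-test, and that test would need 201 rather than 223.

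Finally, a favourable case exists in which only HIIT differs (87–96%), but it sets MICT equal to control and so contradicts hypothesis 1.

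**Conclusion.** The point holds in a limited form. An effect size of unstated metric was entered as f into an F-test whose implied 3 numerator df match neither the three-group effect nor the 2 × 3 interaction. The stated 0.95 does not describe the HIIT–MICT contrast. Depending on what 0.28 means, unadjusted power for that contrast is 23–42% (d), 36–58% (three-group f, equal spacing) or 82–94% (two-group f). Without adjustment it reaches 95% only when MICT is taken as equal to control.

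The results assume 72 to 80 per arm, two-sided alpha between 0.05/3 and 0.05, and equal variances. Baseline adjustment would raise them by an amount that depends on a correlation the document does not give. The df error alone is harmless to the trial, since 201 is below 223. The consequential gap is that one undefined number permits anything from 23% to 94% for a named hypothesis.

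**What to change.** Revise the sample size text; no added enrolment is proposed.

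1. State whether 0.28 is d or f, for how many groups and which outcome, and show the conversion.
2. Correct the numerator df and the required N (201 for f = 0.28 with 2 df; 791 if the converted value is f = 0.14), and say which test the 0.95 covers.
3. Give power, or the detectable difference, for HIIT versus MICT and for HIIT versus control at the Bonferroni alpha. Unadjusted, the latter is about 0.54 SD at 80% power with 72 per arm. If baseline adjustment is relied on, state the assumed correlation.

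The cost is a rewritten paragraph and a less favourable stated power for HIIT versus MICT. The Trial status section says recruitment was still under way, so the clarification can precede the results.
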